#### Digital program satisfaction

At the primary endpoint, satisfaction with the app in the intervention group and satisfaction with the digital psychoeducation flyers in the control group will be assessed using an 11-item measure adapted from previous digital research [50]. This measure is completed by the child and will assess their satisfaction, experience, and perceived helpfulness of the intervention. The first eight items assess participants’ satisfaction and experience with the Sleep Ninja app by asking participants to indicate their agreement or disagreement with each statement. Additionally, participants are asked to rate the overall helpfulness of the intervention on a 5-point scale, ranging from Extremely Unhelpful (1) to Extremely Helpful (5). The final two free response questions examine how Sleep Ninja, or the digital psychoeducation flyers were helpful (e.g., In what ways did Sleep Ninja help you?), and another giving participants the opportunity to provide suggestions for improvement (e.g., What would make Sleep Ninja better?).

#### Intervention adherence and attrition

At the primary endpoint, treatment adherence (to Sleep Ninja) will be assessed using an 11-item, parent-report measure in the intervention group only. The first five items are rated on a 7-point Likert scale from Strongly Disagree (1) to Strongly Agree (7) and assess the child’s use (e.g., My child used Sleep Ninja more than once a week) and changes to behaviour (e.g., My child went to bed at the same time at night and woke at the same time in the mornings). Item 6 asks how many training sessions were completed by the child, with the option to select from 1 to 6. The remaining items assess the degree of parent involvement in the intervention, including frequency and duration of involvement, visits to the parent website, and a free response item allowing parents to describe how they supported their child’s use of the Sleep Ninja app. Data automatically collected within the app will also be used to provide objective measures of app usage, such as whether the app was downloaded, the number of sessions completed, and total time spent using the app. The number of users interacting with the parent webpage and the number of visits per user will be obtained from Google Analytics 4. For participants allocated to the control condition, access to the psychoeducation flyers will be recorded for each participant via URL clicks. Attrition is operationalised as non-completion of the outcome measures and will be reported for each assessment occasion.

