### Intervention condition

Participants allocated to the intervention condition receive access to the child-adapted version of Sleep Ninja for 6 weeks. Sleep Ninja is an automated smartphone application co-designed with 12- to 16-year-olds and parents to deliver CBT-I. It is free and publicly available in Australia on devices using iOS and Android operating systems. The program includes six sequential modules (referred to as ‘training sessions’), a sleep tracking function, sleep scheduling based on required wake time and age-dependent sleep duration recommendations, personalised wind-down routines and reminders, a series of sleep tips, and general information about sleep. Each training session covers a core CBT-I strategy including: (a) sleep scheduling; (b) stimulus control strategies; (c) sleep hygiene for evenings and daytime; (d) cognitive therapy including how to deal with thoughts that can prevent sleep onset (e.g., repetitive worrying) (e) identification and planning for high-risk situations and diversions from sleep routine; and f) relapse prevention. Sessions are delivered through an automated chat-bot where the Ninja acts as a sleep coach. Sleep Ninja is designed to be used during the day and not at bedtime to prevent device use and blue light interfering with sleep. The child version of Sleep Ninja also includes a website for parents, designed in collaboration with parents. The website contains guidance to assist parents in supporting their child to use Sleep Ninja autonomously and additional resources including information on Sleep Ninja, case examples, frequently asked questions, and contact information for the Child Sleep team at the Black Dog Institute. Parents of participants allocated to receive the intervention will be provided with the URL for the website alongside instructions on how to download Sleep Ninja. Child participants allocated to the intervention condition will be instructed to complete the Sleep Ninja app content by undertaking one ‘training session’ and tracking their sleep for three nights per week (approximately 10 min in duration) for six weeks. One email and one Short Message Service (SMS) reminder will be sent to the parents of participants who fail to download the Sleep Ninja app within 7 days of randomisation. Participants who do not download the app will remain in the trial and be included in the intention-to-treat analyses.

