### Data collection, management, and statistical methods

Participant data will be collected and securely stored on the University of New South Wales (UNSW) OneDrive which are hosted on servers provided by the UNSW at GovDC Data Centres in Sydney, Australia. The data is stored in a SQL Server 2016 database, which undergoes daily backups and is supported by 128-bit encryption. To ensure participant confidentiality, at the data analysis stage, each participant will be assigned and only identified by a unique identification code.

For analyses, all study data will be exported from the Qualtrics Survey Platform to SPSS Version 26 using a Microsoft Excel file format. Files with identifiable data will be stored on UNSW OneDrive and once deidentified by authorized members of the research team for analysis will be stored on a secure sever. Any personally identifiable information, such as participant names, email addresses, mobile phone numbers, IP addresses, free response data, will be removed from the outcomes analysis file. Only the research team listed on the project will have access to identifiable study assessment data, while aggregate deidentified data will be retained for future evidence synthesis.

Analyses will be conducted to determine the effect of the interventions on insomnia symptoms at the primary and secondary endpoints. Analyses will be undertaken on an intention-to-treat basis, including all participants randomised, regardless of the intervention received. The effectiveness of the trial intervention will be established using mixed-model repeated measures (MMRM) analyses due to the inclusion of participants with missing data with this approach. The primary hypothesis will be evaluated by a contrast evaluating change in child-reported insomnia symptoms between baseline and 6-weeks post-baseline (primary endpoint), based on the interaction between time and condition. The same approach will be used for secondary outcomes. Adherence and acceptability of the intervention will be described.

Exploratory analyses will compare proportion of young people who meet criteria for MDD at the tertiary endpoint, as well as those showing significant symptoms of depression, operationalised as a t-score of greater than 65 on the RCADS.

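### The parent-report count of completed sessions is described as running from 1 to 6, so it cannot show a child who completed none and is biased upward

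*Protocol article*

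**What the plan says.** The section on intervention adherence and attrition states that at the primary endpoint "treatment adherence (to Sleep Ninja) will be assessed using an 11-item, parent-report measure in the intervention group only". Within that measure, "Item 6 asks how many training sessions were completed by the child, with the option to select from 1 to 6". The app itself has six training sessions, so the upper limit fits; the described range simply starts at 1.

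The same section adds a second source. Data collected automatically in the app will give "objective measures of app usage, such as whether the app was downloaded, the number of sessions completed, and total time spent using the app".

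The section on the intervention condition provides for reminders to parents when the app has not been downloaded within 7 days of randomisation, and then states: "Participants who do not download the app will remain in the trial and be included in the intention-to-treat analyses".

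On use of the data, the section on statistical methods says only: "Adherence and acceptability of the intervention will be described". The article states no adherence threshold and no per-protocol set.

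**The concern.** The plan treats non-use as a real possibility and, rightly, does not remove non-users. They stay in the intervention arm, and their parents are invited to the 6-week assessment like everyone else. Neither the text nor the note to Table 1 limits the adherence measure to families who downloaded the app. A child who downloads it but finishes no session is also a true zero.

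For all of these children, item 6 as described lacks the correct answer. Whether the parent picks the lowest option or skips the item, the summary moves the same way, towards more sessions. At stake is one descriptive result that the trial intends to report. A mean or distribution of parent-reported sessions would look better than it was, and no answer to the item could reveal that a child never started.

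**Working it through.** **Setting the passages side by side**

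1. Options described for item 6: 1 to 6 (section on intervention adherence and attrition).
2. Values that can occur: 0 to 6, because non-downloaders are foreseen and retained (section on the intervention condition).
3. Who is asked: the intervention arm at 6 weeks, with no stated restriction to users (same adherence section; note to Table 1).

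The described options therefore omit one value that the plan itself expects. The article gives no figure for sessions completed, so there is none to reproduce.

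**Size of the bias**

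Inputs, both assumed because the article gives neither:

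- p, the share of responding parents whose child completed no session: 5% to 30%.
- m, the mean number of sessions among children who completed at least one: 3 to 5.

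Formulas:

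- True mean = (1 − p) × m + p × 0 = (1 − p)m.
- Mean if every zero is entered as 1 = (1 − p)m + p. Excess = p.
- Mean if every zero is left blank = m, since only users contribute. Excess = m − (1 − p)m = pm.

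Results for m = 4:

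| p | True mean | Entered as 1 | Left blank | Excess (1) | Excess (blank) |
|---|---|---|---|---|---|
| 5% | 3.80 | 3.85 | 4.00 | 0.05 | 0.20 |
| 10% | 3.60 | 3.70 | 4.00 | 0.10 | 0.40 |
| 20% | 3.20 | 3.40 | 4.00 | 0.20 | 0.80 |
| 30% | 2.80 | 3.10 | 4.00 | 0.30 | 1.20 |

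The p = 20% row in full: the true mean is 0.8 × 4 = 3.2; entered as 1 it is 3.2 + 0.2 = 3.4; left blank it is 4.0.

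Over the whole assumed range the excess is 0.05 to 0.30 sessions if zeros are entered as 1. If they are left blank it runs from 0.05 × 3 = 0.15 to 0.30 × 5 = 1.50 sessions. If some parents enter 1 and others skip, the mean falls between the two cases.

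**Uptake**

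The true share with at least one session is 1 − p, which is 95% to 70% over the assumed range. Among parents who answer item 6 the recorded share is 100% whatever p is, because no lower answer is described.

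**What does not move**

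The app-logged count has a natural zero and carries none of this bias. The primary analysis is an intention-to-treat mixed model for repeated measures on child-reported insomnia, and no adherence variable is described in it.

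**The case against.** The strongest reply is that the trial does not depend on item 6. The app records download status and sessions completed, and the 7-day reminder implies that download status is known for each family. A non-downloader whose parent answers 1 or skips the item can be found from that record. This stands, and it limits the point to the parent-report item.

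Three stronger readings are tempting, and the article supports none of them.

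- A reader might infer that non-users are classed as adherent. No threshold is given, and 1 of 6 is the lowest use that the item can record.
- A reader might infer that the trial's adherence as a whole will be overstated, or cannot be checked against the logs. The objective count is already planned and identifies the non-users.
- A reader might infer that the intention-to-treat result will be interpreted against an inflated dose. The section on blinding mentions completion rates but does not say that they come from item 6, and no dose-response or complier analysis is described.

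It can also be said that other items in the same questionnaire capture non-use: the first five "assess the child’s use (e.g., My child used Sleep Ninja more than once a week", to take the example shown. This helps only in part. Disagreeing with that statement does not separate no use from occasional use, so it does not restore a count of zero.

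Finally, a journal article condenses a questionnaire. A filter question or a *none* option on the full form cannot be ruled out. That is a reason to allow confirmation as an alternative to change. It does not remove the point, because the article states the range and does not merely leave it out.

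**Conclusion.** The point holds for the parent-reported session count alone. As described, item 6 cannot represent a child with no completed sessions, and any summary of it is biased upward by p sessions (zeros entered as 1) or pm sessions (zeros left blank). Both p and m are assumptions here, as is the pattern of parents' answers; the direction of the bias does not depend on their values so long as some responding parents have a child with zero sessions. The conclusion also assumes that the form matches its description in the article.

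No effect estimate, test or sample size changes. Severity is minor: a free improvement to one descriptive result.

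**What to change.** 1. Add a *0 / did not download* option to item 6, or confirm that the form already has one and correct the description.
2. State that the in-app session count, with non-downloaders set to 0, is the main adherence figure, and that item 6 supplements it.
3. If data collection is too far advanced to change the survey, keep step 2 and report item 6 only for children whom the app log shows completed at least one session, saying so in the table.

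The cost is one response option and one sentence. No new data are needed, because the app log is already planned.

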### Sample size

The total sample size required for detecting change in the primary outcome at the primary endpoint was calculated to be 214. This was based on using α = 0.05, power = 0.8 to detect a medium between-group effect size (d = 0.41) [17, 22] on child-reported insomnia outcomes. This estimate accounts for an attrition rate of 40% between baseline and the primary endpoint. The effect size parameter used in the power calculation accounts for potential effects of the active control condition, as seen in the adolescent study [17], but is more conservative than the between-group effect size reported in that study (d = 0.41) due to the differences in the delivery format (parent-supported vs. self-directed).

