## Methods/design

### Trial design

A two-arm randomised controlled trial (RCT) with an equal allocation ratio will compare Sleep Ninja to an active control group. Outcomes include both parent- and child-reported measures, which will be assessed at baseline, post-intervention (primary endpoint, measured at 6-weeks post-baseline), three-month follow-up (secondary endpoint, measured at 3-months post-baseline), and 9-month follow-up (tertiary endpoint, measured at 9-months post-baseline). The University of New South Wales is the sponsor of this clinical trial and ethics approval was provided by the University of New South Wales Human Research Ethics Committee (HC#230070). This trial was prospectively registered with the Australian New Zealand Clinical Trials Registry on the 30th of May 2023 (ACTRN12623000587606) and has been allocated the Universal Trial Number U1111-1294-4167.

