### Strengths

This is the first randomised controlled trial to evaluate app delivered CBT-I in children under 12 years with frequent sleep disturbance. The intervention under evaluation provides a brief, self-guided and time efficient treatment, which is a treatment option for sleep not currently available for 10 to 12 year olds. The trial design includes an active control condition that allows evaluation of the effect of Sleep Ninja beyond non-therapeutic effects, such as knowledge gained from generic sleep information widely available online and parental engagement. The sample size (N = 214) will ensure adequate power to detect intervention effects on insomnia. Finally, this study improves on previous studies by assessing diagnostic criteria for MDD. Although base rates of depression in this age group are low [56, 57], using diagnostic criteria as assessed by the KSADS-COMP goes beyond symptom measures and ensures the sample in this study do not have a history of depression, thereby allowing exploration of the notion that treating sleep reduces risk of subsequent depression.

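### The stated inputs (d = 0.41, 80% power, alpha 0.05, 40% attrition) call for about 317 children, not 214; on those inputs 214 gives about 63% power

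*Protocol article*

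**What the plan says.** All the inputs are in the Sample size section of the protocol article, apart from the allocation ratio, which is under Trial design.

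- Result: "The total sample size required for detecting change in the primary outcome at the primary endpoint was calculated to be 214".
- Error rates and effect: alpha 0.05 and "power = 0.8 to detect a medium between-group effect size (d = 0.41") on child-reported insomnia.
- Attrition: "This estimate accounts for an attrition rate of 40% between baseline and the primary endpoint". The 214 is therefore the number randomised, not the number analysed.
- Justification of the effect: the planning value allows for an effect of the active control and "is more conservative than the between-group effect size reported in that study (d = 0.41").
- Allocation: "A two-arm randomised controlled trial (RCT) with an equal allocation ratio".
- Primary analysis, under Data collection, management, and statistical methods: a mixed model for repeated measures, with "a contrast evaluating change in child-reported insomnia symptoms between baseline and 6-weeks post-baseline (primary endpoint), based on the interaction between time and condition".

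The sample size text gives no sidedness, no named test and no correlation between baseline and follow-up. The Strengths section then relies on the result: "The sample size (N = 214) will ensure adequate power to detect intervention effects on insomnia".

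**The concern.** There are two faults in the same short section. First, the printed inputs do not lead to the printed sample size, and the gap is too large to be rounding. Second, the same value of d appears as the planning effect and as the earlier effect that the planning effect is said to be smaller than. A value cannot be more conservative than itself, so at least one of the two figures is wrong or the sentence is.

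The calculation supports the primary hypothesis at the primary endpoint, and recruitment is to stop when the required number is reached. If the power claim is overstated, a null primary result would be read as evidence against an effect from an adequately powered trial, when the chance of missing an effect of the stated size is close to twice what the reader was told.

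**Working it through.** **Inputs.** Alpha 0.05, power 0.80, d = 0.41 and 40% attrition (Sample size); 1:1 allocation (Trial design). Assumption: two-sided test, because sidedness is not stated.

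**1. Attempt to reproduce 214 from the stated inputs.** The normal approximation per arm is n = 2(z₀.₉₇₅ + z₀.₈₀)²/d² = 2(1.960 + 0.842)²/0.41² = 93.4, so 94. The exact t-test calculation gives 94.35, so 95.

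- Completers: 2 × 95 = 190.
- Randomised: 190/(1 − 0.40) = 316.7, so 317 (314 by the normal approximation).

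The stated 214 is 103 fewer, about a third short.

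**2. Power that 214 delivers.** 214 × 0.6 = 128.4, so about 64 per arm. The noncentrality is d√(n/2) = 0.41 × √32 = 2.32. The t-test power is 0.634 (0.640 by the normal approximation). The effect detectable with 80% power is d = 0.50.

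| True d | Power, 64 per arm |
|---|---|
| 0.50 | 80% |
| 0.41 | 63% |
| 0.40 | 61% |
| 0.35 | 50% |
| 0.30 | 39% |

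The values below 0.41 are illustrative. They show what a planning effect truly smaller than 0.41 would imply; the article names none.

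**3. What does give 214.** For d = 0.50 the t-test needs 63.77, so 64 per arm; 128/0.6 = 213.3, so 214.

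**4. Other routes at d = 0.41.**

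| Route | Randomised |
|---|---|
| Two-sided, divide by 0.6 | 317 |
| Two-sided, multiply by 1.4 | 266 |
| One-sided (75 per arm), divide by 0.6 | 250 |
| One-sided, multiply by 1.4 | 210 |
| Two-sided, no attrition | 190 |

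The one-sided route multiplied by 1.4 comes near 214 but does not reach it. It needs an unstated one-sided test together with a wrong inflation formula, and it would leave about 75% one-sided power with 128 completers. Working backwards, 214 supports 190 completers only if attrition is 1 − 190/214 = 11%, not 40%.

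**5. Baseline adjustment.** Suppose d is standardised on the raw 6-week SD. Adjustment for baseline multiplies the required number by 1 − r², where r is the baseline-to-6-week correlation.

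| r | Randomised needed, 190(1 − r²)/0.6 | Power with 64 per arm |
|---|---|---|
| 0.3 | 288 | 67% |
| 0.5 | 238 | 76% |
| 0.57 | 214 | 80% |
| 0.6 | 203 | 82% |

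For a pure change score the factor is 2(1 − r). At r = 0.5 there is no gain (63%), at r = 0.6 power is 73%, and r of about 0.66 is needed for 80%.

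**6. Direction of the sentence on conservatism.** A planning d below 0.41 raises the requirement: d = 0.40 needs 100 per arm, and 200/0.6 gives 334. The value that reproduces 214, d = 0.50, is above 0.41 and so less conservative. Neither change makes both the sentence and 214 correct.

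**The case against.** The strongest reply is that 63% is not a property of the trial but of an unadjusted, two-sided comparison of completers. The primary analysis is a mixed model of change from baseline, which can gain precision from the baseline measurement, and a condensed article may have left out an assumed correlation. With r near 0.57 the stated design would reach 80%. This stands as a condition on the 63%. It does not rescue the text: the section lists its inputs and no correlation is among them, so none can be credited to the calculation, and the gain is smaller still if the contrast behaves like a simple change score.

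A second reply is that the origin of 214 is not settled. The article never prints 0.50, and the earlier study is not available to show which 0.41 is wrong. If 0.50 was the intended planning value, then the sample size and power agree and the printed d is the slip. This also stands: the use of 0.50 is an inference from an exact match, helped by the word medium. But on that reading the sentence on conservatism is wrong in direction, unless the earlier study's figure is misprinted too. On every reading the section as printed needs correction.

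**Conclusion.** The concern holds. On the stated inputs, with an unadjusted two-sided t-test and equal arms, 317 children are needed, and 214 gives about 63% power at d = 0.41 instead of 80%. A one-sided test would still need 250 and would have about 75% power with 214. What 214 delivers at 80% power is d = 0.50. Only an unstated baseline correlation of about 0.57 (about 0.66 for a pure change score), or attrition near 11%, would make 214 sufficient at d = 0.41. The contradiction between the two uses of 0.41 needs no calculation and holds regardless of these assumptions.

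**What to change.** Keep 214 and restate what it delivers. In the Sample size section, name the test and its sidedness and say that with 214 randomised and 40% attrition, leaving about 64 per arm, the trial has 80% power for d = 0.50 and about 63% for d = 0.41 in an unadjusted two-sided comparison. If the original calculation did assume a baseline-to-follow-up correlation, give its value, its source and the formula instead, and show that they lead to 214.

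State the planning effect and the earlier study's effect as two separate values, checked against the source, and delete or correct the claim that the first is more conservative. Under Strengths, replace the unqualified statement of adequate power with the effect size for which it is true.

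The cost is wording only. No participants are added and neither design nor analysis changes, but the stated power at d = 0.41 becomes less favourable unless a correlation is documented.
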